## Abstract

**Background:**

A significant increase in eating disorder (ED) service waitlists has been observed in the past several years, exacerbating existing barriers to care (eg, long waitlists, scarcity of treatment centers, and positive beliefs surrounding pathology). Given that treatment delays have important clinical correlates (eg, entrenchment of ED pathology), exploring new methods of mental health service delivery for this population is of critical concern. App-based motivational interviewing (MI) delivered prior to the start of treatment has the potential to improve accessibility by simultaneously addressing structural (eg, travel costs) and individual (eg, low motivation) barriers to care. Despite the potential benefits, there remains a lack of empirically validated, ED-specific MI-based mobile apps. Evaluating the feasibility and acceptability of such interventions is a crucial first step before progressing to full-scale efficacy trials.

**Objective:**

This multiphasic mixed methods study aims to develop and assess the feasibility and acceptability of MI-Coach: ED, a novel app designed to increase motivation among women waitlisted for ED treatment. Specifically, this study seeks to determine participant engagement levels, user satisfaction, and perceived usability of the app, as well as to explore preliminary trends in motivation and ED-related symptoms following app use.

**Methods:**

Phase I adapted the content and interface of an existing app based on evidence-based principles (MI-Coach) for an ED population. Phase II pilot tested the app through a pre-post evaluation. Participants (n=30) aged 18 years and older were recruited from ED treatment waitlists in British Columbia, Canada. After completing baseline assessments evaluating demographic and clinical variables (eg, motivation, eating pathology, depression, and anxiety symptoms), participants were provided access to MI-Coach: ED for 1 month. Participants completed postintervention assessments and provided both quantitative and qualitative feedback on the app. Feasibility will be evaluated through the total number of participants recruited, study dropout rates, and engagement indicators (eg, modules completed) within the app. Acceptability will be assessed through self-report measures and semistructured exit interviews, which will explore user experiences, perceived benefits, and barriers to app engagement. Additionally, exploratory analyses will examine changes in motivation and ED symptoms before and after the intervention.

**Results:**

The MI-Coach: ED app has been developed, and recruitment was initiated in November 2022 and terminated in May 2024. Results are being analyzed and will be submitted for publication in May 2025.

**Conclusions:**

This study has the potential to transform ED service delivery and mitigate the impacts of existing treatment barriers for this population. By leveraging a digital MI-based intervention, MI-Coach: ED could serve as a scalable and accessible pretreatment tool, helping to bridge the gap between initial help-seeking and formal ED treatment. Findings from this study will inform the refinement of the intervention and recruitment strategies for future large-scale efficacy trials.

**International Registered Report Identifier (IRRID):**

DERR1-10.2196/66298

## Introduction

Eating disorders (EDs) are serious, life-threatening psychological illnesses that involve disturbances surrounding body image, emotion regulation, and eating behaviors [1,2], resulting in a number of deleterious health consequences and high levels of psychiatric comorbidity [3-5]. Despite the severity of these disorders, ED populations are significantly less likely to access mental health services compared to those with other disorders [5,6]. For instance, wait times exceeding 12 months for ED-specific services have been reported in Ontario, Canada, and nonprofit organizations have observed a 2-fold increase in requests for peer-support services following the COVID-19 pandemic [7]. In this regard, several treatment barriers have been identified limiting access to ED treatments and services. As EDs require specialized forms of care, treatment centers are typically few in number, necessitating significant travel time and associated costs (eg, costs related to travel and childcare and loss of income due to sick leave), and often resulting in long waitlist durations [6]. Further, ambivalence regarding treatment is common among ED populations, with motivation for recovery often in conflict with other factors, such as engaging in ED behaviors to cope with difficult emotions or to provide a sense of control [8-10].

Unfortunately, treatment delays are associated with adverse outcomes, such as reductions in pretreatment levels of motivation and poorer long-term prognosis. Early intervention has been associated with improved treatment outcomes following discharge, longer durations between relapses, and improvements in related psychological symptoms such as depression and anxiety [11]. Recent efforts to bridge treatment barriers and improve outcomes for this population include the delivery of brief interventions such as motivational interviewing (MI) prior to the start of formal treatment. Initially developed by Miller and Rollnick [12] to address ambivalence within substance use treatment, MI is a person-centered approach that aims to strengthen the individual’s intrinsic motivation to change [13]. A recent systematic review conducted by Denison-Day et al [8] found substantial support for the use of MI interventions for individuals with EDs, with a majority (74%) of the studies reviewed reporting significant and long-term improvements in motivation as a result of MI interventions compared to passive interventions, such as psychoeducation. Broadly, studies report that brief MI interventions lead to improvements in motivation, self-esteem, depressive symptoms, and positive treatment outcomes (eg, greater engagement in treatment), particularly when delivered prior to the start of formal treatment [14-16].

Despite the potential for pretreatment MI interventions to address individual treatment barriers, they are typically conducted through in-person, face-to-face sessions [8,14,16,17]. In-person interventions may not adequately address structural treatment barriers, such as costs and scarcity of treatment providers. In order to address this issue, internet and communications technology (ICT)–based interventions have been proposed as a low-cost and accessible form of delivering ED interventions [5,18-20]. Apps in particular show potential in the delivery of pretreatment MI interventions, as they are easy to use, require low effort, and become habitual over time. Further, unlike other ICT-based interventions, they have high hedonic motivation (ie, they are enjoyable to use), which increases their use and adoption [21,22]. In addition, the digital components embedded within apps (eg, modules, graphic design, and diverse multimedia content) have been shown to significantly improve adherence to interventions and reduce dropout rates [23].

Despite preliminary findings suggesting that apps may be an acceptable means of delivering ED services, there is a paucity of effective, evidence-based apps available for use [24-27]. Most publicly available app interventions are based on CBT and behavioral self-monitoring principles but demonstrate limited efficacy compared to traditional delivery methods [24,28]. However, considering the accessibility of apps and their wide adoption in various health and social contexts [29], they may be an effective mode of delivery for pretreatment MI contexts. Help-seeking individuals waiting for formal services likely do not have access to in-person treatment options, despite their urgent need for services. Further, as they have not yet started formal ED treatment, receiving a pretreatment MI intervention may significantly improve treatment outcomes. For example, such interventions may increase motivation to stay on the waitlist and adhere to treatment once services are received [30]. An app-based MI intervention thus has the potential to simultaneously address structural and individual treatment barriers. Despite the potential benefits, to date, no research has investigated the use of app-based MI pretreatment interventions for EDs.

The proposed study aims to adapt and pilot-test MI-Coach, a widely available app-based MI platform, for individuals on ED treatment waitlists. Created by Resiliens Inc, MI-Coach is an evidence-based self-help app developed in collaboration with a registered clinical psychologist. The app was adapted for use within an ED pretreatment context. Furthermore, this will be the first study to investigate whether an app-based MI pretreatment intervention improves clinical symptoms, motivation for treatment, and openness to change for individuals while they wait for ED treatment.

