### Study Design

The current pilot test evaluation follows a naturalistic pre-post design. A pilot test framework was chosen to assess the initial feasibility and acceptability of the app and to identify any potential issues with the study design and delivery format prior to evaluating the app’s efficacy at a larger scale [32]. The MI-Coach: ED app was designed to improve motivation in women-identifying people waiting for formal ED treatment and will be pilot-tested in the province of British Columbia, Canada. Qualitative and descriptive data were collected to determine the acceptability and feasibility of the MI-Coach: ED app.

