### Outcomes and Measures

The primary outcomes that will be evaluated are the overall acceptability and feasibility of the MI-Coach: ED (Multimedia Appendix 3)*.* Feasibility will be assessed through attrition rates throughout the study period, frequency of app use, and module completion. Acceptability will be assessed through qualitative and quantitative feedback from participants through semistructured interviews and self-reports. Additionally, exploratory analyses will be conducted regarding the impacts of the MI-Coach: ED app on motivation and associated clinical characteristics.

Self-reported demographic data, including gender identity, age, level of education, ethnicity, and socioeconomic status were collected using Qualtrics, a web-based and secure data collection platform. Additionally, clinical data (ie, weight and height, history of ED treatment, age of ED onset, presence of cognitive difficulties, sensory deficits, history of traumatic brain injury, other mental health comorbidities, and ED waitlist experiences) was collected. The Sick, Control, One, Fat, and Food questionnaire [43], a brief screener that identifies the presence of common ED symptoms, was used to determine eligibility prior to enrollment. Clinical characteristics (ie, eating pathology, recovery motivation, body dissatisfaction, depression, and anxiety symptoms) were evaluated through several self-report questionnaires administered at baseline and posttest, including the Eating Disorder Examination Questionnaire (EDE-Q) [44], the Readiness and Motivation for Change Questionnaire (RMQ) [45], the Body Shape Questionnaire (BSQ) [46], the Patient Health Questionnaire-9 (PHQ-9) [47], and the 7-item General Anxiety Disorder Scale (GAD-7) [48]. Additionally, technological literacy was evaluated at baseline using the Mobile Device Proficiency Questionnaire [49] and the eHealth Literacy Scale [50].

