The subsequent pilot-test portion of the study consisted of a four-week period during which participants used the app in a naturalistic way. Following study completion, participants were compensated CAD $10 (≈US $7.10) for each study portion completed (ie, baseline questionnaire package, onboarding session, posttest questionnaire package, and exit interview), receiving up to CAD $40 (≈US $28.41) through the Tango Card rewards platform. To reduce the impact of possible confounds (eg, financial motivation), participants were informed that their compensation would not be impacted by their app use during the pilot test phase and that there are no minimum requirements for app use. Once the pilot test was completed, a second brief consent form (Multimedia Appendix 5) and posttest questionnaires assessing self-reported clinical features (ie, the EDE-Q, RMQ, PHQ-9, GAD-7, and BSQ) and feedback regarding the app (ie, the adapted TAM-Q and uMARS) were completed. Finally, participants were invited to participate in a videoconferencing-based exit interview to provide additional feedback on their experience with the study author. The semistructured interview guide (Multimedia Appendix 6) was used as an outline to standardize the interview process across participants [52].

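### The article states causal aims for motivation and symptoms that a single-group pre-post design cannot answer, and carries the resulting effect sizes into planning a randomized trial

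*Protocol article*

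**What the plan says.** Three places in the protocol article state or imply a causal aim.

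- Introduction: "this will be the first study to investigate whether an app-based MI pretreatment intervention improves clinical symptoms", and likewise motivation and openness to change.
- Methods, Hypotheses: perceived usefulness and ease of use are expected to raise engagement, which in turn is expected to improve outcomes. A second hypothesis is that motivation to recover will rise after app use.
- Methods, Outcomes and Measures: "exploratory analyses will be conducted regarding the impacts of the MI-Coach: ED app on motivation and associated clinical characteristics".

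Other places are more restrained.

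- Methods, Study Design: "The current pilot test evaluation follows a naturalistic pre-post design". No comparator is described.
- Methods, Sample Size Estimation: the focus is acceptability and feasibility, not efficacy.
- Abstract, Objective: the clinical part is limited to exploring early trends.

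Two further statements matter. On the course without the app, the Introduction says "treatment delays are associated with adverse outcomes, such as reductions in pretreatment levels of motivation and poorer long-term prognosis", and the abstract's Background links delay to entrenchment of pathology. On later use, the Conclusions section of the Discussion plans to take effect size estimates from the exploratory analyses into power calculations for a full-scale randomized trial.

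**The concern.** Whether an intervention improves an outcome is a question about the difference between what happened with it and what would have happened without it. The study observes only the first. Reading pre-post change as the app's effect assumes that nothing would have changed over four weeks of waiting, and the article's own background gives reason to doubt that.

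Two things are at stake. One is what the report may conclude about motivation and symptoms. The other is the next trial: if the single-arm change is used as the expected treatment effect, that trial may be wrongly sized.

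**Working it through.** **No figure to reproduce.** The sample of 30 was chosen pragmatically. The article gives no alpha, power, effect size or standard deviation, and says no formal calculation was made. The check is therefore one of identification.

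**Decomposition.** For any scale scored so that higher is better, write the expected pre-post change as

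D = δ + B, with B = w + m + c,

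where δ is the app effect, w is change due to waiting, m is regression to the mean, and c is the effect of contact and repeated measurement. One arm estimates D only. Equating D with δ requires B = 0.

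**What the article says about each part of B.**

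- w: delay is associated with lower motivation (Introduction) and entrenched pathology (Abstract, Background). Both are unfavourable. Neither comes with a size or a time scale.
- m: entrants are help-seeking volunteers screened for ED symptoms, and one recruitment route reaches people newly added to a waitlist (Participant Recruitment; Outcomes and Measures). Some regression is plausible. Its size is not given.
- c: each participant has a telephone screening, a video onboarding session and repeated questionnaires (Outcomes and Measures). The size is not given.

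**Consequence for each result.**

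- D > 0 fits δ > 0, and equally fits δ = 0 with B > 0.
- D = 0 fits δ = 0 with B = 0, and equally fits a benefit offset by decline (δ = −B, B < 0) or a harm offset by improvement (δ = −B, B > 0).

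So neither improvement nor absence of change identifies δ.

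**Do the planned analyses supply B?** Statistical Analysis names the Jacobson-Truax classification and exploratory growth curves. The first compares each person's change with a reliable-change criterion and a clinical cutoff. The second models individual trajectories. Neither contains a reference course without the app. More participants would estimate D more precisely and leave B unchanged.

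**Consequence for the randomized trial.** A between-group effect is δ = D(app) − D(control). The single-arm D equals it only if the control arm would not change. Sample size per arm is proportional to 1/δ², so planning on D instead of δ gives a trial (δ/D)² times the size needed. For a real benefit, that is too small if B > 0, and too large if B < 0 with D still positive.

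**Use of the app.** Participants were told that "there are no minimum requirements for app use", so whole-group change may include people who used it little or not at all. Statistical Analysis lists logged modules, days, exercises and logins. The Hypotheses section posits a link between engagement and outcome, but the article describes no display of one against the other.

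**The case against.** The primary outcomes are feasibility and acceptability, which need no comparator, and a single-arm pilot is a legitimate design for them. The clinical analyses are labelled exploratory. The abstract's Methods and the Statistical Analysis section speak of change before and after, and efficacy is deferred to a larger study. On this view only loose wording remains. The absence of a use-by-change display may reflect condensation, since a fuller analysis plan could hold it. The lack of a minimum use requirement is deliberate and explained.

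Most of this stands, and it limits the point to the stated aims and the later use of the estimates. It does not remove the point: calling an analysis exploratory concerns how firm its conclusions are, not whether change may be credited to the app.

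Four stronger readings are tempting and unsupported.

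- A reader might put a size on regression to the mean and infer that an interval for mean change could exclude zero with no app effect. The documents give neither the entrants' distance from a long-run mean nor a test-retest correlation, and the article names no test or interval for mean change.
- A reader might infer that background drift runs in opposite directions for motivation and symptoms. The abstract's Background points to unfavourable drift in pathology too.
- A reader might expect counts of reliably improved participants to be reported as the app's impact. No section says so.
- A reader might conclude that unchanged motivation should be read as possible benefit. The cited association has no size or time scale. The Introduction mentions waits of more than 12 months, whereas this study lasts four weeks. A rule protecting only null results would be one-sided.

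**Conclusion.** The point holds as a mismatch between stated aims and design. The Introduction, Hypotheses and Outcomes and Measures sections pose causal questions that the single-group design cannot answer and that sit badly with the abstract's Objective and with Sample Size Estimation. Change in either direction cannot be attributed to the app, and the effect sizes foreseen in the Conclusions section are not between-group effects.

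The size of the non-app component is unknown, and so is its net direction. The conclusion needs no assumption about either, only that zero background change is not established. The article does not establish it, and its own background suggests otherwise. The design itself is not at fault, and no control group is asked for.

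**What to change.** 1. In the Introduction, Hypotheses, and Outcomes and Measures, restate the clinical aim as: describe change in motivation and symptoms over 4 weeks of app access while waitlisted. Recast the engagement hypothesis as an association to be described.
2. State that change in either direction, or its absence, is not attributed to the app.
3. In the Conclusions section of the Discussion, state that the single-arm change will not serve as the between-group effect for powering the randomized trial. The variability, retention and engagement data can inform that trial.
4. Show each participant's change against logged module use, labelled descriptive and confounded, because people who use the app more may differ in other ways. This addresses the engagement hypothesis without resolving attribution.

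The article reports recruitment closed and analysis under way, so the same wording can be carried into the results report. The cost is a few sentences, one figure from data that the plan already obtains, and a more modest claim.

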## Methods

### Hypotheses

This project is guided by the technology acceptance model (TAM), which theorizes that an ICT’s acceptability is determined by its perceived ease of use and usefulness [31]. It is thus hypothesized that greater perceived usefulness and ease of use of the MI-Coach: ED app will lead to greater use and engagement with the app, and subsequently, improved treatment outcomes. It is also hypothesized that participants will experience an improvement in their motivation to recover from an ED following use of the app. In addition, the app’s acceptability and feasibility will be examined, as well as the possible impacts of other clinical variables (eg, depression, anxiety, BMI, and ED severity) on motivation to recover.

### Ethical Considerations

Ethics approvals were granted by the University of British Columbia Okanagan Campus’ Behavioral Research Ethics Board (H22-02046) on October 4, 2022, and by the Vancouver Coastal Health Research Institute (V22-02046) on October 10, 2023. All eligible participants provided informed consent electronically through the secure web-based platform Qualtrics prior to enrollment, after receiving detailed information about study procedures, potential risks and benefits, data confidentiality, and voluntary participation. Participants were informed of their right to withdraw from the study at any time without penalty. Participant privacy was maintained by storing data on password-protected university servers accessible only to research personnel. All identifying information was stored separately from the study data. Participants received compensation of up to CAD $40 (≈US $28.41) in the form of digital gift cards. Compensation was clearly outlined in the informed consent form and was structured to avoid influencing participation or app use.

### Study Design

The current pilot test evaluation follows a naturalistic pre-post design. A pilot test framework was chosen to assess the initial feasibility and acceptability of the app and to identify any potential issues with the study design and delivery format prior to evaluating the app’s efficacy at a larger scale [32]. The MI-Coach: ED app was designed to improve motivation in women-identifying people waiting for formal ED treatment and will be pilot-tested in the province of British Columbia, Canada. Qualitative and descriptive data were collected to determine the acceptability and feasibility of the MI-Coach: ED app.

